### *BRCA1* and *BRCA2* genetic testing

The coding sequences and intron/exon boundaries of BRCA1 and BRCA2 are analyzed by sequence analysis (primer sequences available on request). Gross deletions and duplications in the BRCA1 gene are detected by multiplex ligation-dependent probe amplification (MRC-Holland, Amsterdam, kit P002-C2). All findings are confirmed by an independent test.

### Intervention

Patients who choose the DNA-direct procedure, receive a home informational package including an informational letter, a link to a website including a short educational movie about hereditary breast cancer and DNA-testing. Also included are two EDTA blood vials with informed consent and family history forms. Patients are instructed to call their family doctor assistant to ask where to have their blood drawn, then return the vials plus signed forms in the appropriate return package. An appointment for a personal consultation to disclose results is set 8 weeks after DNA-testing has commenced.

All patients (whether they choose DNA-direct or DNA-intake) are seen by one of five selected genetic counselors, each of whom has extensive experience in genetic counseling for hereditary cancer. These counselors have had multiple meetings in order to structure the DNA-direct consultations as follows: If no mutation is found, further screening advice is formulated based on familial risk scores: FHAT [43], Myriad [44] and Claus/van Asperen [45,46]. Further evaluation of family history and features of other hereditary cancer syndromes may be required. In the case of a pathogenic *BRCA1* or *BRCA2* mutation, this result is disclosed immediately, first allowing the patient to react, followed by an explanation of the consequences, including prevention measures and family evaluation. If considered necessary, a second consultation is offered for further genetic counseling. All confirmed *BRCA1/2* carriers will be approached by a social worker to extend psychosocial support if needed, as in usual care.

### Study outcomes

Participants are asked to fill out a questionnaire twice: at baseline and following the conclusion of genetic counseling and/or testing (follow-up). Some measures are used in both questionnaires, while others are only included in either baseline or follow-up.

### Primary outcomes

#### Choice of procedure

Percentages of patients choosing one procedure over the other (ratio between the two groups) is determined to assess the desirability of the new DNA-direct procedure.

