## Methods/design

### Design

The study examines the effect of the DNA-direct procedure on the experience and psychological distress of patients with breast cancer as well as several secondary outcome measures, including waiting and processing times, as compared to the current DNA-intake procedure. Two groups will be compared: the intervention group, who choose to undergo the DNA-direct procedure, and the control group, who will receive care as usual (DNA-intake procedure). Participants may choose freely between the DNA-direct versus DNA-intake procedures. This study is not randomized due to the wish to evaluate whether there is indeed a desire for the proposed DNA-direct procedure amongst patients with breast cancer, and to evaluate the reasons stated for preferring one procedure over the other.

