### Study sample

All female patients previously or currently diagnosed with breast cancer and referred to the department of Clinical Genetics of the Radboud University Nijmegen Medical Centre from August 9th 2011 are eligible for inclusion. Recruitment will continue until the desired total of 150 participants is reached. Patients who have problems reading Dutch text, problems with family communication or problems of psychological/psychiatric nature (including current use of related medication) will be excluded.

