### Recruitment

Patients are sent a written letter by a trained doctor announcing a phone call, in which the two choices of procedure are explained (DNA-intake for a face-to-face intake consultation prior to DNA-testing, versus DNA-direct for a home package of telephone, written and digital information) and exclusion criteria are checked. The aim of this telephone approach is triage: by checking for exclusion criteria such as psychological problems, patients who aren’t deemed suitable for DNA-direct (due to its dependency on the patient’s own decision making ability) are filtered out and instead invited for a regular intake consultation, where further psychosocial support is immediately available prior to DNA-testing. Genetic counseling is not offered by phone: questions of this nature are deferred to the personal consultations. The triage phone call has been thoroughly practiced (over 20 times) by the involved doctor with people both specialized and not specialized in clinical genetics.

All patients receive the same two questionnaires, one at inclusion (baseline) and one after completion of the chosen genetic counseling procedure (follow-up). Patients who are confirmed carriers of a *BRCA1/2* mutation, patients reporting problems with the chosen procedure, and randomly selected (n = 10) patients will be invited for a 30 min semi-structured telephone interview.

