### Sample size calculation

For this intervention study, participants are not randomized into groups, but given their own choice. This leads to certain complications when it comes to a formal power calculation. First, the ratio between the two procedures is unknown: this may either be balanced (50% versus 50%) or unbalanced (e.g. 20% versus 80%). Second, due to not randomizing, the results will have to be corrected for multiple confounders, which are not all known at this point. The sample size, based on aforementioned ratio between both groups (choice of procedure), needs to be large enough to be able to integrate these confounders into a regression model. Using a power of 80% and a two-tailed probability level for statistical significance testing of 0.05, while taking into account group ratios ranging from balanced (50% versus 50%) versus unbalanced (to an estimated maximum of 20% versus 80%), the total sample size has been set to 150 patients with breast cancer.

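### Uptake of DNA-direct is defined as the ratio between the two enrolled groups, so eligible women who hear the choice but do not join are uncounted and the percentage may overstate uptake by an unknown amount

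*Protocol article*

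**What the plan says.** The first item under Primary outcomes in the protocol article is Choice of procedure: "Percentages of patients choosing one procedure over the other (ratio between the two groups) is determined to assess the desirability" of DNA-direct.

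Three other places show what the two groups are:

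- Design: "Two groups will be compared: the intervention group, who choose to undergo the DNA-direct procedure, and the control group", who receive care as usual. The same section gives the free choice of procedure to participants.
- Study sample: "Recruitment will continue until the desired total of 150 participants is reached".
- Sample size calculation: the size is described as "based on aforementioned ratio between both groups (choice of procedure"), so group ratio and choice are again treated as the same quantity.

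The purpose is wider. The Design section explains that randomization was given up partly to "evaluate whether there is indeed a desire for the proposed DNA-direct procedure amongst patients with breast cancer", and partly to learn the reasons for preferring one procedure. The source population under Study sample is "All female patients previously or currently diagnosed with breast cancer and referred to the department of Clinical Genetics" of the centre from August 2011, subject to the exclusions.

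The Recruitment section says that a telephone call explains both procedures and checks the exclusion criteria. Women found unsuitable for DNA-direct "are filtered out and instead invited for a regular intake consultation". The article does not say how many eligible women are expected to decline the study, what care they then receive, or whether DNA-direct can be had without joining.

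**The concern.** The quantity wanted is how many eligible women, offered both procedures, would take DNA-direct. The quantity defined is the split among those who also agreed to be studied. The two agree only if nobody declines, or if decliners would choose as participants do.

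There is a reason to doubt the second condition. DNA-intake is the existing procedure, so a woman who prefers it may see no procedural gain in joining, and joining brings a baseline and a follow-up questionnaire. DNA-direct is new. The Discussion adds that it allows blood to be drawn for testing from women who would not normally meet the testing criteria, whereas DNA-intake does not offer them the test. If women who prefer intake join less often, the enrolled ratio leans toward DNA-direct.

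At stake is the reading of the first-listed primary outcome, which is also one of the two stated reasons for not randomizing. A larger sample narrows the interval but leaves this error in place.

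**Working it through.** **Inputs from the article.** Total enrolled: 150. Anticipated group split: from 50:50 to at most 20:80. The article states no expected uptake for DNA-direct and no number approached or declining, so there is no uptake figure of the plan's own to reproduce.

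**Assumed inputs.** u = share of the 150 choosing DNA-direct, taken as 60% for illustration and as 20%, 50% and 80% to cover the article's range. q = share of eligible women offered the choice who decline the study, taken as 0–30%.

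**Formulas.**

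- Eligible women offered = 150 / (1 − q).
- Uptake if all decliners receive intake (lower bound) = u × (1 − q).
- Preference if all decliners would have wanted DNA-direct (upper bound) = u × (1 − q) + q.
- 95% half-width of the enrolled percentage = 1.96 × √(u(1 − u)/150).

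**At u = 60%, i.e. 90 of 150:**

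- q = 0: 90/150 = 60%; no change.
- q = 10%: 150/0.9 = 167 offered; 90/167 = 54%; upper bound 54 + 10 = 64%.
- q = 20%: 150/0.8 = 188 offered; 90/188 = 48%; upper bound 48 + 20 = 68%.
- q = 30%: 150/0.7 = 214 offered; 90/214 = 42%; upper bound 42 + 30 = 72%.
- Half-width: 1.96 × √(0.6 × 0.4/150) = 7.8 points.

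**Across the range (lower–upper bound, %):**

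| Enrolled uptake u | q = 10% | q = 20% | q = 30% | 95% half-width (points) |
|---|---|---|---|---|
| 20% | 18–28 | 16–36 | 14–44 | 6.4 |
| 50% | 45–55 | 40–60 | 35–65 | 8.0 |
| 60% | 54–64 | 48–68 | 42–72 | 7.8 |
| 80% | 72–82 | 64–84 | 56–86 | 6.4 |

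If decliners go to intake, realised uptake is overstated by the factor 1/(1 − q): 1.11 at 10%, 1.25 at 20% and 1.43 at 30%. At u = 60% the drop is 6, 12 or 18 points, so from 20% decline onward it exceeds the sampling error of 7.8 points. The upper bounds show that preference, unlike realised uptake, can also lie above the enrolled figure.

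**The case against.** The definition speaks of patients rather than participants, and the choice is put to patients in the triage call, so it could cover everyone who voiced a choice. This reading is possible but weak. The parenthesis in the definition and the sample size section both equate choice with the group ratio, the Design section says that participants choose, and the article also uses patients for those who fill in the questionnaires.

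A second objection is that refusal counts and screening logs are details that an article leaves to the full protocol. That is fair for the log itself, and its absence is not the point. The point is the denominator that the article does state.

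The strongest objection concerns direction. A reader might infer that desirability is overstated as a matter of fact. The documents do not support this. They do not say that decliners exist, that they receive intake, or that DNA-direct depends on enrolling. A woman may also refuse the questionnaires and still want DNA-direct. This objection stands: the direction for realised uptake is a plausible inference, and the direction for preference is open.

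A reader might also infer that women excluded at triage distort the desirability figure. They do not. The exclusion rule sends them to intake, so their attendance there says nothing about what they wanted.

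Finally, the abstract names satisfaction and psychological distress as the primary outcomes and does not list uptake. This tempers the stakes, but uptake still stands first under Primary outcomes in the body.

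**Conclusion.** The concern holds in a limited form. The stated denominator, the enrolled 150, does not match the stated purpose, which is desire among patients with breast cancer. The enrolled-only percentage may overstate uptake among eligible women offered the choice, by an amount that the article gives no means of estimating.

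The illustrative fall from 60% to 54–42% rests on three assumptions: an enrolled uptake of 60%, a decline rate of 10–30%, and intake for every decliner. At zero decline there is no effect. Treating every decliner as preferring intake gives a lower bound and not a best estimate; at 60% enrolled uptake and 20% decline, preference is only known to lie between 48% and 68%.

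**What to change.** Define the uptake denominator as all eligible women offered the choice at the triage call. For each call, log eligibility, stated choice and participation, kept as anonymous counts. Report the percentage choosing DNA-direct with a 95% confidence interval.

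Where a woman who declines the study states a preference, count it. Where she does not, show decliners separately, with a lower bound (all intake) and an upper bound (all DNA-direct). Do not count them all as intake. Report what care decliners received.

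Report women excluded at triage as a flow count that describes reach, outside the desirability estimate. Keep the ratio of the enrolled groups as a description of the comparison sample.

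The cost is one logged line per call that is already being made, with no extra patients or visits. The uptake figure may turn out less favourable or, once bounds are shown, less precise. If few women decline, the log will show that the concern is small.

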#### Psychological burden (baseline and follow-up)

##### Quality of Life

To measure global health-related quality of life (QoL), two items scored on a scale of 1-7 were selected from the EORTC-Q30. The full EORTC-Q30 has been widely used and validated for cancer research [47]. The two global QoL items have an excellent internal consistency as proven by the reported Cronbach’s α of 0.91 [48].

##### General health

The 12-item version of the General Health Questionnaire (GHQ-12) is used as a measure of general psychological distress, using GHQ-scoring of 0,0,1,1 per item (range 0-12) with a threshold of ≥4 to identify ‘caseness', recommended for patients with breast cancer. The GHQ-12 is the shortest version of all GHQs and recommended for research use, with good internal consistency (Cronbach’s α = 0.82 - 0.86) [49-51].

##### Cancer specific distress

The Impact of Event Scale (IES) measures cancer specific distress [52,53] and is included in baseline once using genetic predisposition for cancer as the distressing event, once using breast cancer. For follow-up, only genetic predisposition is included. The IES consists of 15 items, each scored 0,1,3,5. A total score of 9-25 or ≥26 reflects moderate or serious adaptation difficulties respectively. The Dutch version of the IES has a good internal consistency with a Cronbach’s α of 0.87 to 0.96 [53].

##### Risk perception

Risk perception of a genetic predisposition for breast cancer, as well as breast cancer recurrence, is measured on a scale of 0-100.

##### Cancer worry scale

To measure fear of cancer recurrence, the 8-item Cancer Worry Scale (CWS) is included, which has previously been used in studies among cancer patients. Each item is scored 1,2,3,4 from 1 ‘almost never’ to 4 ‘almost always’, the total score ranging from 8-32. It has a good internal consistency with a Cronbach’s α of 0.80 [54-56].

#### Experiences with genetic counseling (follow-up)

##### Decisional conflict

The difficulty of decision-making, in this study defined as whether or not to undergo genetic testing, is assessed using the traditional format of the Decisional Conflict Scale; 1 item (“I expect to stick to my decision”) is left out as it is not applicable to DNA-testing [57-59]. 15 items scored 0,1,2,3,4 from 0 ‘strongly agree’ to 4 ‘strongly disagree’ remained, including “I am satisfied with my decision” which is also used separately for overall satisfaction. Scores are summed, divided by 15 and multiplied by 25, resulting in a range from 0 to 100. Scores below 25 are considered as ‘no decisional conflict’, between 25 and 37.5 as ‘moderate conflict’ and exceeding 37.5 as ‘severe conflict’. The DCS has good internal consistency exceeding 0.78 [57-59].

##### Satisfaction with choice

Knowledge of hereditary breast cancer following versus prior to the chosen genetic counseling procedure, as well as the amount and quality of information received, is rated on a scale of 1-6. Participants answer ‘yes’, ‘no’ or ‘don’t know’ for choosing DNA-testing and/or DNA-direct if given a second chance or asked to give advice to other women in a similar situation.

##### Satisfaction with genetic counseling

The Dutch National Institute for Public Health and the Environment (RIVM) developed a standard questionnaire to measure satisfaction with the service (18 items) and information (8 items) expected of a genetic counselor. Each item is scored on a Likert-scale 1-4, total scores range from 26-104. Open-ended questions evaluate positive/negative experiences during the chosen genetic counseling procedure.

### Secondary outcomes

#### General information (baseline)

##### Demographical and breast cancer information

Data are gathered on age, education level, work status, marital and parental status, cancer status, medical information need (scale 1-10), use of breast cancer information resources and type of information previously given by their referring physician.

##### Empowerment (baseline)

Empowerment is the process in which patients discover and utilize their own power, which will be measured using the Cancer Empowerment Questionnaire (CEQ). It consists of 40 items, each scored on a Likert-scale of 1-5 (1 ‘strongly disagree’, 5 ‘strongly agree’). Four factors are identified: ‘Personal Strength’, ‘Social Support’, ‘Community’ and ‘Health Care’. A good internal consistency (Cronbach’s α = 0.94) was demonstrated for all four factors and the total Empowerment scale [60].

#### Experiences with genetic counseling and testing (follow-up)

##### Choice of procedure

Participants describe reasons for choosing DNA-direct or DNA-intake.

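### Patients' own reasons for choosing a procedure, one of two stated grounds for not randomising, are asked only at follow-up, and knowledge before the procedure is recalled rather than measured.

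*Protocol article*

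**What the plan says.** **Why there is no randomisation.** The Design section of the protocol article gives two grounds. The first is demand: "This study is not randomized due to the wish to evaluate whether there is indeed a desire for the proposed DNA-direct procedure". The second is the wish "to evaluate the reasons stated for preferring one procedure over the other".

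**When things are asked.** Study outcomes describes two questionnaires, one at baseline and one once counseling and/or testing has ended. It adds: "Some measures are used in both questionnaires, while others are only included in either baseline or follow-up". The section headings then show which measure belongs to which time point.

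**Reasons for choice.** Under Secondary outcomes, within the block on experiences with counseling and testing that is marked as follow-up: "Participants describe reasons for choosing DNA-direct or DNA-intake".

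**Knowledge.** Under Satisfaction with choice, in the other experiences block, also marked as follow-up, the participant rates on a 1-6 scale "Knowledge of hereditary breast cancer following versus prior to the chosen genetic counseling procedure".

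**Decisional conflict.** In that same follow-up block, the scale addresses "The difficulty of decision-making, in this study defined as whether or not to undergo genetic testing".

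**When the choice is offered.** Recruitment says the two procedures are explained in the triage telephone call, and that the baseline questionnaire is given at inclusion.

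**The concern.** A study that lets patients choose, partly in order to learn why they choose, should record the reasons when the choice is made. Here they are recorded at the end. By then the patient knows whether the procedure went smoothly, how the counselor handled disclosure and, if tested, whether a mutation was found. A patient content with the outcome can report different reasons from those that moved her at the time, and the data give no way to tell the two apart.

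The planned adjustment is also at stake. The Statistical analysis section corrects for self-selection by regressing follow-up results on group with baseline results as covariates. A knowledge value that exists only as a recollection after counseling is not a baseline result. It was formed after the exposure whose effect is being estimated.

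**Working it through.** No figure in the article depends on this point, so the check is a mapping of items to time points, followed by a small calculation of what follow-up loss would remove.

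**1. Where each item sits**

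| Item | Baseline | Follow-up |
|---|---|---|
| Quality of life, GHQ-12, Impact of Event Scale (genetic predisposition), risk perception, Cancer Worry Scale | yes | yes |
| Demographics, information need and sources, empowerment | yes | no |
| Self-stated reasons for choice | no | yes |
| Knowledge, after versus before | no | yes |
| Decisional Conflict Scale | no | yes |

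The placement comes from the section headings. It is a stated allocation, not a detail left open by a condensed article.

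**2. Order of events.** The choice is offered at the triage call and the baseline questionnaire comes at inclusion. The procedure follows, then any DNA result, then the follow-up questionnaire. For DNA-direct, the Intervention section sets the disclosure consultation 8 weeks after testing starts, so these patients recall their reasons across at least that interval. The article states no such interval for DNA-intake. A DNA-intake patient who is not tested has no wait between testing and disclosure.

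**3. Can hindsight differ by group?** The article's Discussion says DNA-direct patients can be tested even if they do not meet the usual criteria, whereas DNA-intake patients who do not meet them are not offered a test. The share of patients tested, and the mix of results, can therefore differ between groups when the reasons are written down. The article gives no figure from which to size this.

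**4. Is there another source of the reasons?** The triage call explains the options and checks exclusion criteria; nothing says that it records reasons. The telephone interviews cover mutation carriers, patients who report problems and 10 randomly selected patients, and are not described as taking place at the time of choice.

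**5. Loss of reasons.** The choice is known for everyone included; the reason is known only for those who return the follow-up form. The article states no loss rate, so a range of 10-20% is assumed.

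- All patients: 0.10 × 150 = 15 and 0.20 × 150 = 30 choices without a reason.
- Smaller group at the most unbalanced split in the Sample size calculation (20% versus 80%): 0.20 × 150 = 30 patients. With the same loss rate in both groups, 0.10 × 30 = 3 and 0.20 × 30 = 6 are missing, which leaves 27 to 24 sets of reasons for the less chosen procedure.

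**6. Knowledge.** Write the recalled prior rating as true prior rating + recall error, and the gain as after − recalled prior. If the mean recall error differs by δ between groups, the group difference in gain is shifted by −δ. Nothing collected in the study would allow δ to be estimated, because no rating is made before the procedure. If the item is instead a single comparative rating, there is no separate prior value at all. Either way, the regression has no baseline term for knowledge.

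**The case against.** **The reasons are not the whole case for free choice.** A reader might infer that the stated justification for not randomising collapses. It does not. The other ground, whether DNA-direct is wanted, is answered by the choice itself, which is listed under Primary outcomes and needs no follow-up form. The reasons are a descriptive secondary item, and the study hypothesis does not rest on them. Demographics, information need and empowerment are measured at baseline, so determinants of choice can still be studied. All of this stands, and it limits the point to the self-stated reasons.

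**Decisional conflict.** It is tempting to call the timing of the Decisional Conflict Scale a third error of the same kind. The article does not support that. The scale concerns the decision to be tested, not the choice of procedure, so it has no bearing on the argument about randomisation. One of its items also serves as the measure of overall satisfaction, which belongs after completion. Collecting it before disclosure would probably mean different settings for the two groups and would miss patients who decline or are not offered testing. Its timing is a trade-off.

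**Knowledge.** The item can be read as perceived change, and a separate baseline rating has its own weakness, since a patient's internal standard may shift once she is informed. This is fair. It makes the baseline rating a complement to the follow-up item, not a replacement. It does not supply the missing covariate.

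**Follow-up loss affects every follow-up measure.** True, but the reasons need not be among them, because they exist at inclusion.

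**Conclusion.** The point holds in a limited form. As written, the study collects the self-stated reasons, one of its two grounds for giving up randomisation, only after the procedure and any result. All reason-for-choice data are therefore retrospective. At an assumed loss of 10-20%, 15-30 of 150 choices would also have no reason attached. Hindsight that differs by group is plausible from the differing testing criteria, but its size cannot be derived from the article. The prior-knowledge rating is a recollection and cannot serve as a baseline covariate.

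A reader might infer that the distress comparison is compromised too. It is not: those measures are taken at both time points. Nor should the 8-week interval be read as a minimum for all patients, since it is stated only for DNA-direct. The conclusion assumes that the headings describe the questionnaires as used and that reasons are not recorded elsewhere at the time of choice; the article mentions no such record. The change is worth making because answers given at the time of choice cannot be recovered later.

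**What to change.** 1. Move the reasons-for-choice question to the existing baseline questionnaire, and state that it is completed at inclusion, once the choice is made and before the procedure starts.
2. Add a rating of current knowledge of hereditary breast cancer (1-6) to the baseline questionnaire, and use it as the baseline covariate when follow-up knowledge is analysed. Keep the existing knowledge rating and the items on whether the patient would choose the same again at follow-up.
3. Leave the Decisional Conflict Scale at follow-up with its overall-satisfaction item, and say in the plan that it is a retrospective rating made after any result is known.

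The cost is two more baseline items, one open question and one rating. No extra contact is needed, and the distress measures and sample size are unchanged.
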